## Abstract

Pain in Parkinson’s disease (PD) represents a complex phenotype known to decrease quality of life. This pragmatic randomized, controlled clinical trial evaluated the efficacy of pharmacopuncture (PA) for improving pain symptoms and investigated the corresponding therapeutic mechanisms in patients with PD. Ninety patients with PD-related pain were randomly allocated to receive either PA, manual acupuncture, or usual care in a 1:1:1 ratio; sixty healthy controls were included for comparative analysis of brain imaging data. Over 12 weeks, study treatment provided 2 days per week for 8 weeks with a follow-up period of 4 weeks. The primary outcome measure was the King’s Parkinson’s Disease Pain Scale score for assessing improvement in PD-related pain, including a sub-analysis to investigate the pattern of changes in pain according to a PD-related pain mechanism-based classification. Secondary outcome measures included a numerical rating scale-based assessment of the intensity and location of pain and changes in pain-associated symptoms, such as depression, anxiety, and sleep disorders. Exploratory outcome measures included structural and functional brain patterns on magnetic resonance imaging, blood molecular signature changes, gait analysis, facial expression and movement assessment in response to emotional stimuli, and a traditional Korean medicine syndrome differentiation questionnaire. The trial findings provided important clinical evidence for the effectiveness of PA in the management of PD-related pain and its associated symptoms, and helped elucidate the mechanism of its therapeutic effect on PD-related pain.

## 1. Introduction

The incidence of Parkinson’s disease (PD) is increasing owing to the aging of society. Pain as a non-motor symptom of PD is experienced by a vast majority of patients, with an incidence rate of 40–86%. Furthermore, pain has a remarkable impact on the quality of life of patients with PD, but treatment guidelines often do not take pain into account [1]. The etiology and phenotype of pain in PD are complex and multifactorial [2]; it is classified into five types according to Ford’s scheme—musculoskeletal, radicular-neuropathic, dystonic, central neuropathic, and akathisia pain [3]. Recently, Mylius et al. reported a PD pain classification system with three pain types based on the mechanism of chronic pain: nociceptive pain, such as that in musculoskeletal pain syndromes; neuropathic pain such as radicular or central pain; and nociplastic pain, where the nociceptive system is overactive even without any tissue damage or lesions in the somatosensory system [4]. Most patients with PD experience nociceptive pain such as musculoskeletal pain due to abnormal postures and visceral pain due to abnormal functioning of the vegetative nervous system. Pain management in PD is focused on optimizing dopaminergic treatment related to insufficient dopaminergic supply or dopamine-sensitive central pain. However, pain management therapy is only effective in approximately 30% of PD patients [5]. Therefore, it is necessary to establish the pathophysiological mechanisms and pathways underlying pain in PD using specific evaluation scales that consider the pain type. Moreover, as patients with PD also present with anxiety and depression [6,7], changes in pain-related symptoms in patients with PD also need to be investigated.

Pharmacopuncture (PA) is a traditional medical therapy that involves injecting herbal extracts into acupoints based on pharmacology and meridian theory, and combining herbal medicine and acupuncture to achieve synergistic effects. *Jungsongouhyul* PA is one of the eight principal PAs based on the traditional medicine syndrome differentiation (SD) of *Yin-Yang*, exterior-interior, hot-cold, and deficiency-excess [8]. Specifically, *Jungsongouhyul* PA prescribes extravasated blood treatment involving the herbal drugs *Gardeniae Fructus*, *Corydalis Tuber*, *Olibanum*, *Myrrha*, *Persicae Semen*, *Paeoniae Radix Rubra*, *Salviae Miltiorrhizae Radix*, and *Sappan Lignum* for adjusting the function of the body and improving pathological conditions [9]. It is used to treat various conditions including pain, neurological diseases, and gastrointestinal diseases [10], and is most often applied to manage musculoskeletal disease [11]. Combination therapy that includes *Jungsongouhyul* PA has been found to be demonstrably beneficial for patients with acute traumatic shoulder pain [12] and patients with cervical pain caused by traffic injury [13]; moreover, crush-induced sciatic nerve injury in a rat model was used to show that the neuroprotective effect of combination therapy including *Jungsongouhyul* PA was related to pain reduction and motor nerve recovery, decreased substance-P expression, and increased brain-derived neurotrophic factor expression [14,15]. As such, PA is used to treat pain symptoms and for nerve recovery. The pain in PD is mostly caused by musculoskeletal pain activated by mechanical, thermal, or mechanical stimuli related to nonneural tissues and to increased muscle rigidity. PD pain is also classified as neuropathic pain associated to a lesion or disease of the peripheral or central somatosensory systems [4]. Therefore, PA will help relieve musculoskeletal pain and neuropathic pain in PD. PA has the advantages of a more rapid effect, easier dosage adjustment, and additional synergistic effects from the acupuncture and herbal medicine extracts [11]. Furthermore, PA as a non-pharmacological approach is useful for addressing patient reluctance in terms of increasing pill burden, fear of drug interactions, and poor tolerability or response to analgesics [15]. Therefore, *Jungsongouhyul* PA may be a promising modality for pain treatment in PD.

However, limited clinical trials have assessed the efficacy of *Jungsongouhyul* PA for pain in patients with PD and the corresponding therapeutic mechanisms. Hence, it is difficult to confirm whether *Jungsongouhyul* PA is effective for pain treatment in PD. Recently, SU *Eohyeol* PA with enhanced efficacy was developed by adding *Cervi Pantotrichum Cornu* to *Jungsongouhyul* PA. Herein, we present a study design and trial protocol to evaluate the effectiveness of SU *Eohyeol* PA for pain management in patients with PD. We also aim to elucidate the therapeutic mechanism underlying the effectiveness of PA in patients with PD by analyzing the levels of molecular signatures in the blood and the structural and functional brain patterns on magnetic resonance imaging (MRI).

## 2. Materials and Methods

### 2.1. Aims

To assess the effectiveness and safety of PA for directly improving PD-related pain and pain-associated motor and non-motor symptoms.To investigate, in an exploratory manner, the possibility of neuroimaging and molecular signature indicators as biomarkers of the therapeutic response to PA for PD.To explore the pathogenesis of pain subtypes in PD, as well as the corresponding current therapy guidelines for traditional medicine, such as traditional Korean medicine.

### 2.2. Study Design and Setting

This clinical study was a pragmatic randomized, usual care (UC)-controlled, three-arm trial to investigate the effectiveness of PA for the treatment of pain in patients with PD. PD patients who meet the eligibility criteria will be enrolled and randomly allocated to the treatment group (PA with conventional therapy), manual acupuncture (MA) control group (MA with conventional therapy), or UC control group (UC with conventional therapy). The subjects underwent PA or MA 2 days per week for 8 weeks and were followed up for 4 weeks after treatment. All assessments were performed in the dopaminergic “on” state in patients with PD (at the same time, in each patient after the last session of conventional treatment). The dopaminergic “on” state refers to periods during which symptoms remain adequately controlled in response to dopaminergic medications. A flowchart describing the study design is presented in Figure 1.

The effectiveness of PA was assessed according to improvements in pain and related symptoms, changes in structural and functional brain data, and molecular signature indicators in blood samples. Previous studies have reported that structural and functional network topology on MRI differs between PD patients and healthy controls [16]. Therefore, healthy individuals were enrolled to undergo MRI assessment, and investigated the structural and functional MRI differences between PD and healthy controls. The study setting and site of data collection was the Clinical Trial Center of Kyung Hee University Hospital in Gangdong, South Korea. The study was designed and reported in accordance with the Consolidated Standards of Reporting Trials guidelines and the Standard Protocol Items: Recommendations for Interventional Trials (SPIRIT) checklist (Additional File 1). The protocol was reviewed, revised, and supported by experts on traditional Korean medicine, MRI, statistics, acupuncture, and neurologic disorders in South Korea.

### 2.3. Participant Recruitment

A total of 90 PD patients with pain and 60 healthy participants were recruited by displaying posters in the hospital and community, the internet, local newspapers, and subway advertisements from May 2022 to November 2024. Participants who met the eligibility criteria (Table 1) and provided written informed consent for study participation received information regarding the clinical study during consultation with the coordinator. Subsequently, all PD patients were randomly allocated to the PA, MA, or UC control groups. Healthy participants were individuals with no functional or organ-related diseases or clinically significant findings determined based on their medical history and physical examination.

### 2.4. Randomization

The 90 patients were allocated to the PA, MA, or UC groups in a 1:1:1 ratio by an independent statistician using computer-generated three- or six-block-size randomization. Each participant was selected via systematic sampling and was assigned an identification code enclosed in an opaque envelope. The assessors were blinded to the primary outcome and the Unified PD Rating Scale (UPDRS) II and III scores. In other words, the assessors collecting the data were blinded to the group allocation. The outcomes were evaluated by two assessors, one of whom was blinded and one who was not blinded. The enrollment of participants, allocation sequence, assignment to groups, and assessor blinding were the responsibility of the Clinical Trial Center of Kyung Hee University Hospital.

### 2.5. Interventions

All patients with PD underwent PA or MA therapy twice a week for 8 weeks. Conventional treatments, including L-DOPA, catechol-O-methyl transferase inhibitor, monoamine oxidase inhibitor, and dopamine agonist treatments, were allowed during the trial. For combination drugs, any drugs taken four weeks before participation in the study were allowed at the discretion of the researcher if they were not prohibited drugs (steroids, immunosuppressants, neuropsychiatric drugs) or other drugs that might have affected the results of the study. Analgesic drugs could be continuously taken if the dose had been stable for more than two weeks at the time of screening, but the details of drug administration (name of the drug, purpose of administration, dosage, and duration of administration) were recorded at each visit. In addition, any oriental medical therapy to improve PD pain, other than the intervention being performed in this study, was prohibited. Drugs that could affect symptoms during the period of clinical research were prohibited from being administered at the judgment of the researchers. Procedures, including details of needling (i.e., acupoints centered on the area where the participant complains of pain, needle stimulation, and retention time) to be administered in the PA and MA groups, were performed according to the clinical judgment of a senior Korean medicine doctor with more than 10 years of clinical experience based on the patient’s condition in the pragmatic randomized controlled trial (RCT). All procedural methods were retrospectively recorded. Treatment was discontinued based on the withdrawal of consent by participants or their legal representatives, violation of the eligibility criteria during the clinical trial, occurrence of adverse events (AEs), or poor compliance defined as receiving less than five of the sixteen total treatments.

### 2.6. Treatment Group: PA

The treatment group received SU Eohyeol PA that included the following nine dried medicinal herbs: *Cervi Pantotrichum Cornu* and Jungsongouhyul PA herbs (*Gardeniae Fructus*, *Corydalis Tuber*, *Olibanum*, *Myrrha*, *Persicae Semen*, *Paeoniae Radix Rubra*, *Salviae Miltiorrhizae Radix*, and *Sappan Lignum*). The medicinal herbs were extracted, distilled, and filtered for injection into the acupoints. The final form of the medicinal herb filtrate liquid used for the PA was supplied by the pharmaceutical manufacturer of Namsangcheon Korean Medicine Clinic (Republic of Korea) and was manufactured in compliance with Good Manufacturing Practices in accordance with the Ministry of Food and Drug Safety guidelines.

### 2.7. Control Group: MA or UC

The MA and UC control groups received MA or UC to improve pain and related symptoms in PD.

### 2.8. Outcome Measures

The primary outcome measure was the King’s Parkinson’s Disease Pain Scale (KPPS) score at visits 1 and 18 to evaluate the effectiveness of PA for pain in PD. Pain in PD has been previously divided into three types—PD-directly related pain (related to disease onset), PD-indirectly related pain (aggravated by the disease), and PD-unrelated pain [17]. The KPPS has been validated for PD-directly related pain. As subjects with KPPS score >0 were enrolled in this study, the effectiveness of PA was limited to PD-directly related pain. The secondary outcome measures were the numerical rating scale (NRS) score for pain area and questionnaire survey (UPDRS II and III, Beck Depression Inventory II, Beck Anxiety Inventory, Euro-Quality of Life-5 Dimension, Pain Catastrophizing Scale, and PD Sleep Scale-2) results for related symptoms. To investigate the biological mechanisms underlying PD, exploratory outcome measures included MRI findings, molecular signatures in the blood, SD questionnaire survey, gait analysis, and facial expression analysis based on facial muscle response to emotional stimulation. The schedule for outcome measure assessments is presented in Table 2.

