#### 2.8.1. Primary Outcome: Assessment Scales for PD Pain

The KPPS is a self-reported questionnaire that assesses pain in PD. Fourteen items in seven domains encompass recognized categories of pain in PD: domain 1, musculoskeletal pain; 2, chronic body pain; 3, fluctuation-related pain; 4, nocturnal pain; 5, orofacial pain; 6, discoloration/edema, swelling; and 7, radicular pain. Each item is scored by multiplying the scores of the intensity (0–3) by frequency (0–4), and the total score ranges between 0–144. The KPPS is a reliable and valid scale for grading various types of pain in PD [18]. In addition, the cut-off points for distinction of pain severity levels (no pain, mild, moderate, and severe pain) in PD have been reported for the KPPS [19]. In this study, the total KPPS score, including all seven domains, was measured to assess the improvement of direct PD-related pain.

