## Figures and Tables

**Figure 1 ijerph-20-01776-f001:**
[figure not shown]
Subject selection flowchart. PA, pharmacopuncture; MA, manual acupuncture; UC, usual care; MRI, magnetic resonance imaging; HC, healthy control.

**Table 1 ijerph-20-01776-t001:** Patient eligibility criteria.

Inclusion Criteria
Adult patients (age ≥ 19 years)
Diagnosis of idiopathic PD based on the UK Parkinson’s Disease Society Brain Bank criteria
Hoehn and Yahr Scale stage 1–4
King’s Parkinson’s Disease Pain Scale score > 0
A stable dose of conventional treatment for at least 4 weeks prior to enrollment
Terminated PA or MA treatment 4 weeks before enrollment
Provide voluntary written informed consent to participate in this clinical study

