**Exclusion criteria**
Parkinson-plus syndromes (i.e., multisystem atrophy, progressive supranuclear palsy, corticobasal degeneration, and dementia with Lewy bodies)
Pain unrelated to PD (e.g., postoperative pain)
History of neuropsychiatric disorder unrelated to PD
Moderate or higher cognitive impairment that will interfere with the evaluation of treatment effects
Severe acute cardiovascular disease (i.e., heart failure, myocardial infarction, stroke, and hypertension)
Serious conditions (i.e., anemia, active pulmonary tuberculosis, thyroid disease, and other infectious and systemic diseases)
Active cancer
Uncontrolled hypertension (systolic blood pressure > 160 mmHg or diastolic blood pressure > 100 mmHg)
History of hypersensitivity reactions to PA
Indications for PA treatment being inappropriate or unsafe (i.e., hemorrhagic disease, patients with severe diabetes who have a higher risk of infection)
History of taking oral adrenal corticosteroids (steroids), immunosuppressants, or antipsychotic drugs or other drugs that may affect clinical trial results within the last 4 weeks
Inability to undergo MRI
Pregnant or lactating women or current contraceptive use among women of pregnant potential who are likely to become pregnant (except for women who have undergone sterilization)
History of drug or alcohol abuse
Unstable medical condition as determined by the research clinician; A patient who shows clinically significant diseases and disorders in physical or clinical examination or is receiving active treatment thereof
Participation in another clinical trial within the last 4 weeks
History of vaccination within 4 weeks or plans to be vaccinated during the clinical trial period
Inappropriate for enrollment due to other reasons as determined by the investigator

PD, Parkinson’s disease; PA, pharmacopuncture; MA, manual acupuncture; MRI, magnetic resonance imaging.

**Table 2 ijerph-20-01776-t002:** Schedule of enrollment, clinical outcomes, and safety assessment.

		Screening	MRI	Treatment			MRI	Follow-Up
Week		−2 to −1	−1 to −0	1	4	8	8 to 9	12
Visit No.		1	2	3 (Baseline)	10	18	19	20
Provide informed consent		O						
Identification of inclusion and exclusion criteria		O						
Demographics		O						
Medical and disease history		O						
Vital signs		O	O	O (every visit)	O (every visit)	O	O	O
Clinical laboratory examination		O				O		
Identification of eligibility criteria for MRI measurement		O						
Randomization		O						
Outcome measures	KPPS	O		O	O	O		O

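### The primary outcome starts from Visit 1, Table 2 calls Visit 3 baseline, and randomisation at Visit 1 leaves the Visit 3 pain score and all secondary baselines after allocation

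*Protocol article*

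**What the plan says.** Section 2.8 gives the primary outcome as the King's scale, "KPPS) score at visits 1 and 18 to evaluate the effectiveness of PA for pain in PD". In Table 2, Visit 1 is the screening visit (week −2 to −1) and Visit 3, in week 1, carries the baseline label. KPPS is ticked at Visits 1, 3, 10, 18 and 20. The randomisation row has one tick, "Randomization O", in the Visit 1 column.

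Table 1 requires "King’s Parkinson’s Disease Pain Scale score > 0" for entry. Section 2.3 places allocation after eligibility and consent: "Subsequently, all PD patients were randomly allocated to the PA, MA, or UC control groups". It mentions no wait until Visit 3.

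On who reports and who is masked, section 2.8.1 states "The KPPS is a self-reported questionnaire that assesses pain in PD". Section 2.4 says of the assessors "In other words, the assessors collecting the data were blinded to the group allocation", with this blinding tied to the primary outcome and UPDRS II and III. Masking of patients is not described, and the Discussion explains that the comparator is usual care without a placebo.

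Section 2.11.2 specifies a mixed model for repeated measures with group and visit, plus within-group before-and-after tests. It does not say which visit is the starting point.

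**The concern.** Two KPPS scores could be taken for the baseline. Section 2.8 points to Visit 1 and the label in Table 2 points to Visit 3, and they lie on opposite sides of randomisation. An analyst who follows the table would use a patient-reported score collected one to two weeks after allocation, from a patient who may know the arm. Disappointment at usual care or expectation of pharmacopuncture could then move the starting value differently by arm, and that difference would enter any change score or baseline adjustment. A larger sample would not remove it.

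For the secondary outcomes there is no choice to make. As scheduled, none has a value from before allocation.

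**Working it through.** The plan states no figure on this point, and the sample size does not depend on it. The check is a reading of Table 2 by column, followed by a short calculation under assumed values.

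**Step 1. Order of events in Table 2.**

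| Visit | Week | Title in Table 2 | Relevant ticks |
|---|---|---|---|
| 1 | −2 to −1 | Screening | consent, eligibility, laboratory tests, **randomisation**, KPPS, blood for molecular analysis |
| 2 | −1 to −0 | MRI | MRI, syndrome differentiation, BDI-II, BAI |
| 3 | 1 | Treatment (labelled baseline) | KPPS, NRS, UPDRS II/III, Pain Catastrophizing Scale, EQ-5D, PDSS-2, gait, facial expression, first session |
| 18 | 8 | Treatment | KPPS and the other Visit 3 measures |

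**Step 2. Which side of allocation each score falls on.**
- Visit 1 KPPS: before. Table 2 does not order events within a visit, but the score must exceed 0 for entry and section 2.3 puts allocation after eligibility.
- Visit 3 KPPS: after.
- Secondary outcomes listed in section 2.8 (NRS, UPDRS II/III, BDI-II, BAI, EQ-5D, Pain Catastrophizing Scale, PDSS-2): first measured at Visit 2 (BDI-II, BAI) or Visit 3 (the other five). None of the seven has a pre-allocation value. UPDRS II/III has a blinded assessor; the other six rest on the patient's own report.

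**Step 3. Use of the word baseline.** Section 2.10 speaks of a laboratory examination at baseline, while Table 2 ticks laboratory tests at Visits 1 and 18 only. The article therefore uses the word for Visit 1 in one place and for Visit 3 in another.

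**Step 4. What a shift would do if Visit 3 were used.** Let *b* be the between-arm difference at Visit 3 caused only by knowing the allocation, in SD units. Let *r* be the fraction of it still present at Visit 18, *ρ* the within-arm correlation of Visit 3 with Visit 18 (equal SDs assumed), and Δ the effect free of any shift.
- Change from Visit 3: expected contrast = Δ + *rb* − *b* = Δ − (1 − *r*)*b*.
- Adjusted for Visit 3: expected contrast = Δ + *rb* − *ρb* = Δ − (*ρ* − *r*)*b*.

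With *r* = 0 (shift gone by Visit 18), the absolute bias is *b* and *ρb*:

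| Assumed *b* (SD) | Change score | Adjusted, *ρ* = 0.5 | Adjusted, *ρ* = 0.7 |
|---|---|---|---|
| 0.1 | 0.10 | 0.05 | 0.07 |
| 0.2 | 0.20 | 0.10 | 0.14 |
| 0.3 | 0.30 | 0.15 | 0.21 |

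All values of *b*, *r* and *ρ* here are assumptions; the article gives none of them. If usual-care patients report more pain and pharmacopuncture patients less at Visit 3, the bias would shrink the apparent advantage of pharmacopuncture. With the Visit 1 KPPS as the starting score, *b* = 0 by design.

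**The case against.** The strongest reply is that section 2.8 already settles the primary outcome. It names Visits 1 and 18, and Visit 1 precedes allocation. A label in a table should not outweigh an explicit outcome definition. This stands: as section 2.8 is written, the starting score for the primary between-arm comparison is sound. What remains is the conflicting label in Table 2, the silence of section 2.11.2, and the secondary outcomes.

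It is also fair to say that patient awareness at Visit 3 is inferred. The article does not say when envelopes are opened or when patients are told. The KPPS assessor is blinded, so the exposure comes through the patient's own report. The bias figures in turn describe analyses that section 2.11.2 does not specify, since it names neither a change score nor a baseline covariate. A shift that persists to Visit 18 partly cancels in a change score.

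A reader might infer more than the documents support:
- *Regression to the mean biases the arm comparison if Visit 1 is used.* It does not. The same entry threshold applies to all randomised arms, so its expected effect cancels between them. A threshold of more than 0 on a 0 to 144 scale also selects little on severity. At most it touches the within-group before-and-after tests.
- *The structural MRI baselines are biased.* Those scans do follow allocation, but nothing in the article suggests that one or two weeks of knowing the arm changes cortical thickness, grey-matter volume or diffusion measures.
- *Ineligible patients will be found after randomisation.* The article does not say whether laboratory results are awaited, and section 2.3 describes patients who met the criteria. This is speculation.

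**Conclusion.** The inconsistency is real and should be fixed, but it does not invalidate the primary comparison. Section 2.8 and Table 2 point to different starting visits. The Visit 1 KPPS is a valid pre-allocation score. The Visit 3 KPPS and the first values of all secondary outcomes are post-allocation, with no patient masking described, so the self-reported ones are open to influence from knowledge of the arm.

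The size of that influence cannot be derived from the article. The range of 0.05 to 0.30 SD shown above rests on an assumed shift of 0.1 to 0.3 SD that has disappeared by Visit 18 and, for adjusted analyses, an assumed correlation of 0.5 to 0.7.

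One tempting conclusion must be resisted: simply rewriting section 2.8 to Visits 3 and 18. Unless randomisation moves as well, that would replace a sound starting score with an exposed one and create the very bias at issue.

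**What to change.** **Preferred.** In Table 2, move the randomisation tick to Visit 3, after all baseline assessments and before the first session. Only then define the primary outcome in section 2.8 from Visits 3 and 18, and name Visit 3 as the baseline in section 2.11.2. The secondary outcomes then gain pre-allocation baselines too.

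**For patients randomised at Visit 1, or if randomisation stays there.** Recruitment is dated from May 2022, so this case may already apply.
- Keep the Visit 1 KPPS as the single primary baseline, stated alike in sections 2.8 and 2.11.2. If the schedule changes part-way, the Visit 1 KPPS is pre-allocation for everyone and so is the one score that can serve the whole trial.
- Relabel Visit 3 in Table 2 as the first treatment visit.
- State how the Visit 3 KPPS enters the repeated-measures model, and do not use it as a pre-treatment baseline for between-arm contrasts.
- Report the secondary self-report baselines as collected after allocation.

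If the single tick at Visit 1 misstates actual practice, correct the tick and say when the envelope is opened.

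**Cost.** A short amendment to Table 2 and sections 2.8 and 2.11.2, with no added visits or patients. If randomisation moves, allocation is known one to two weeks later when sessions have to be booked.
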